Many studies have tried to find evidence for effective implementation strategies to improve quality of care. A multifaceted clustered RCT by [name] *et al*. aimed at optimizing GPs' test ordering behaviour by means of local quality improvement collaboratives (LQICs), found a decrease of 8 to 12% in test volumes over a period of six months [7]. This strategy was tested using six topics for continuing medical education (CME). Other studies have tested several implementation strategies to improve test ordering and prescribing behaviour. Passive dissemination of guidelines or recommendations does not seem to influence test ordering behaviour. Audit and feedback have often been used and showed mostly a modest effect in terms of influencing test ordering or prescribing. The effect of audit and feedback on adherence to desired practice ranged from -10% to +68% (median +16%) [8-12]. In other studies, the introduction of a problem-based test ordering form proved to be a promising tool to improve test ordering [7,13-18]. Similar effects on volumes of tests ordered as those in the [name] study have been found for more or less similar multifaceted implementation strategies [19,20]. Small group peer review using direct individual feedback seemed to reduce inappropriate prescribing [12,21,22]. Lagerlov found a 6 to 13% improvement in adherence to guidelines for the prescription of anti-asthmatic drugs and antibiotics for urinary tract infections in an RCT using reflection on guidelines and prescription feedback in small groups [23].

The Cochrane Effective Practice and Organization of Care group (EPOC) systematically reviews studies on implementation strategies to improve quality of care. Their work has generated the general insight that multifaceted strategies are usually more effective than single interventions [12,24], although this was not entirely confirmed by an NHS HTA review by Grimshaw *et al*. [16]. The prevailing insight is that the effect of an intervention is larger when tailored strategies are used and when barriers to and facilitators of change are addressed.

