## Objectives and research questions

### Hypotheses

We expect that the transfer of the strategy of LQICs to stakeholders in the field will be feasible. We hereby hope to create a solid basis for continuation after the end of the study.

We also expect that large-scale implementation, giving attention to both test ordering and prescribing behaviour, will lead to similar changes in performance as those found on test ordering in the trial by [name] *et al*. [7].

Successful implementation will be positively related to the level of group performance of the groups included, in terms of level of attendance, number of meetings, drawing up working agreements, discussing barriers to change, and evaluating working agreements.

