### Sample size

A sample size calculation is not really possible beforehand, because it is not yet known what working agreements will be created and with respect to what tests or drugs. The specific targets, incorporated in working agreements will probably be based on extreme overuse or underuse of certain tests or drugs by some or all group members. It is possible, for instance, that the group will decide to eliminate a particular obsolete test or drug or create a working agreement to decrease or increase the mean volume of tests ordered or drugs prescribed by 20%, from 35% to 55%.

The sample size calculation used in this trial is as follows: to detect an improvement of 20% in a certain target between groups, assuming an ICC of 0.10 [5], an alpha of 0.05 and a beta of 0.1 and a mean group size of seven, 44 LQICs would be needed. Anticipating a dropout of 10%, we would need to recruit 50 groups. A population this large would account for approximately 900,000 registered patients.

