#### Effect evaluation

1. The volumes of particular tests ordered and particular drugs prescribed for which the group has agreed that change, either decrease or increase, would be necessary.

2. The total volumes of tests ordered and drugs prescribed by the participating GPs for the clinical topics chosen.

3. The inter-physician variation in test ordering and prescribing behaviour for the clinical topics chosen.

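### On the inputs printed, a beta of 0.1 and 44 LQICs do not agree: 44 groups give about 80% power for 35% versus 55%, and 90% needs 58 to 60

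*Protocol article*

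**What the plan says.** The Sample size section first says that a calculation is hardly possible in advance, because the working agreements are not yet known. As an illustration, it describes a group that might agree to "decrease or increase the mean volume of tests ordered or drugs prescribed by 20%, from 35% to 55" per cent. It then gives the calculation actually used: "to detect an improvement of 20% in a certain target between groups", "assuming an ICC of 0.10", "an alpha of 0.05 and a beta of 0.1 and a mean group size of seven, 44 LQICs would be needed". Allowing 10% for dropout, 50 groups are to be recruited. Whether the test is one- or two-sided is not stated, nor is any allowance for baseline adjustment.

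Under Effect evaluation, the first outcome is the volume of tests and drugs "for which the group has agreed that change, either decrease or increase, would be necessary". The second is total volumes and the third is inter-physician variation. The Analysis section plans a multilevel analysis of covariance of volumes with baseline data as a covariate. Proportions from prescribing indicators are a repeat analysis, done if they are available.

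**The concern.** The inputs and the result are printed side by side, so the sum can be checked, and on its plain reading it does not come out. If beta is 0.1, the group count is too low by about a quarter. If the group count is right, the unadjusted type II error for that difference is about twice the stated one. The trial sets its recruitment from this figure. A reader of a null result would also take the stated 10% as the chance of having missed a 20-point effect.

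There is a second problem, of scale. A move from 35% to 55% is a change of 20 percentage points in a proportion, or 57% in relative terms (20/35). The text calls it a 20% change in mean volume. The outcomes are volumes, and under Hypotheses the strategy is expected to produce changes in performance similar to those of an earlier trial, which, according to the Background, "found a decrease of 8 to 12% in test volumes over a period of six months". No power is stated on that scale.

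**Working it through.** **Inputs from the Sample size section.** Rates 0.35 and 0.55 (the only pair given); alpha 0.05; beta 0.1; ICC 0.10; seven GPs per group; dropout 10%.

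**Assumptions.** Two-sided test, because targets may go up or down; equal allocation to the two arms; no baseline adjustment, because none is stated.

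**Design effect.** 1 + (7 − 1) × 0.10 = 1.6.

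**Formulas for GPs per arm, before the design effect.**
- Unpooled: n = (z_α + z_β)² × [p₁(1 − p₁) + p₂(1 − p₂)] / (p₁ − p₂)²
- Pooled: as above, but with z_α multiplying √[2p̄(1 − p̄)], where p̄ = 0.45, and z_β multiplying √[p₁(1 − p₁) + p₂(1 − p₂)]

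Groups per arm = n × 1.6 / 7, rounded up.

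**Attempt to reproduce 44 at the stated beta of 0.1.**
- Unpooled: (1.960 + 1.282)² × (0.2275 + 0.2475) / 0.04 = 124.8. Then 124.8 × 1.6 / 7 = 28.5, so 29 per arm and **58 in total**.
- Pooled: 127.9. Then 127.9 × 1.6 / 7 = 29.2, so 30 per arm and **60 in total**.

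44 is not reproduced.

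**Same inputs at beta 0.2.**
- Unpooled: 93.2 per arm, 21.3 groups, so 22 per arm and **44 in total**.
- Pooled: 95.9 per arm, 21.9 groups, so 22 per arm and **44 in total**.

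**Power at fixed numbers of groups, 35% versus 55%, two-sided, unadjusted.** The effective number of GPs per arm is (K/2) × 7 / 1.6 for K groups.

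| Groups | Power, pooled | Power, unpooled |
|---|---|---|
| 44 | 80% | 81% |
| 50 (all retained) | 85% | 86% |
| 58 | 90% (89.8%) | 90% |
| 60 | 91% | 91% |

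With 44 groups, 35% versus 58% (23 points) gives 90% power pooled and 91% unpooled.

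**Other routes to 44 at beta 0.1.**
- *One-sided alpha 0.05:* 48 groups under both formulas. One-sided power with 44 groups is about 88% (pooled).
- *Other variants, two-sided:* the arcsine formula gives 58.6 groups before rounding, a cluster-level t calculation 60, and the continuity correction 64.
- *20% read as relative (35% to 42%):* more than 460 groups.
- *Different ICC or group size:* an ICC of about 0.035, or about 12 GPs per group, would give 44. Both contradict the stated inputs.
- *Other 20-point pairs:* 40 versus 60% needs 58 to 60 groups, 50 versus 70% needs 56 to 58, and 20 versus 40% needs 50. Further from the middle, 15 versus 35% and 65 versus 85% need 44 (unpooled) to 46 (pooled), and 70 versus 90% needs 38. The section names none of these pairs.
- *Baseline adjustment by the factor 1 − r²:* with r = 0.5, 57.0 × 0.75 = 42.8 (unpooled) and 58.5 × 0.75 = 43.9 (pooled), so 44 in equal arms. With r = 0.4 the need is 48 to 50, and with r = 0.6 it is 38. No r is stated.

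**Dropout step.** 44 / 0.9 = 48.9, so 49, rounded up to 50. This step is sound. The same step takes 58 to 65 and 60 to 67.

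**The case against.** The strongest reply is that beta 0.2 is not the only explanation of 44. The plan is to analyse covariance with baseline data. A baseline correlation of 0.5 reduces the 90% requirement to 44 just as exactly, because 0.75 is also very nearly the ratio of the 80% to the 90% requirement. In addition, 35% and 55% are offered only as an illustration, the calculation sentence gives no base rate, and pairs such as 15 versus 35% come to 44 to 46 at beta 0.1. The section itself warns that the calculation is tentative.

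Part of this stands. The printed text cannot show which input produced 44, so it does not prove that the intended beta was 0.2. A reader might also infer that the trial in fact runs at a 20% type II error. The documents do not support that: the planned analysis is a baseline-adjusted multilevel model of volumes, and its power could be higher than that of an unadjusted comparison of two proportions.

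What does not stand is that this rescues the printed figure. No correlation and no other pair of rates is stated, and the calculation claims no credit for either. The warning does not settle the matter, because the article goes on to give the calculation used and recruits from it.

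A second tempting reading is to put 8 to 12 points into the same model and report a low power for the hypothesised effect. That would turn a relative fall in test volume into percentage points of a proportion. The documents give no SD for volumes, so power for that effect cannot be computed from them.

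**Conclusion.** The concern holds as an inconsistency in the stated calculation. With 35% versus 55%, ICC 0.10, seven GPs per group, equal arms and two-sided alpha 0.05, beta 0.1 requires 58 to 60 LQICs, which is 14 to 16 more than stated. The printed 44 corresponds to 80 to 81% unadjusted power, or to 90% power for about 23 points. A one-sided test narrows the gap (48 groups) but does not close it.

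The conclusion rests on taking the section's example as the base rate and on no baseline adjustment. It concerns what the article states, and is not an estimate of the power of the final analysis. The scale error is separate and depends on none of these assumptions: the effect is described as a percentage change in mean volume but is a difference between two proportions, and the stated power does not address a percentage change in volume.

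**What to change.** Keep recruitment at 50 groups and make three changes to the Sample size section.

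1. Restate the power: 44 LQICs give about 80% power (beta 0.2) for 35% versus 55%, or 90% for a difference of about 23 points, two-sided and without baseline adjustment. If 44 was derived with a baseline correlation or with other base rates, print that input instead, so that beta 0.1 and 44 reconcile. State the sidedness in either case.
2. Describe 35% to 55% as a 20-percentage-point change in a proportion, not as a 20% change in mean volume.
3. Add the detectable percentage change in volume, using the SD, ICC and baseline correlation from the t = 0 extracts that the Measurements section already plans, and set it beside the 8 to 12% found in the earlier trial.

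The cost is wording and one calculation on baseline data. Design, recruitment and analysis are unchanged. The drawback is that, unless a further input is documented, the stated power becomes less favourable.

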### Randomization

LQIC groups will be randomized as such (cluster randomisation). The intervention is aimed at these groups. Pre-randomization stratification will be performed on group size and level of group performance using a pre-randomization questionnaire [See additional file 1] prior to the intervention. The levels of group performance are as determined by DGV [28]. This level is a known confounder for an effective intervention on medical education among groups of GPs [30,31]. After stratification, all groups within a stratum will be randomly allocated to either arm A or arm B (Figure 1).

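### On the only rates printed (35% to 55%), the sample size inputs need 58 to 60 LQICs at beta 0.1 with two-sided alpha; the stated 44 is the number for beta 0.2

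*Protocol article*

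**What the plan says.** In the protocol article, Sample size, the first paragraph warns that a calculation is hardly possible in advance because the working agreements are not yet known. As an example of an agreement it names one to "decrease or increase the mean volume of tests ordered or drugs prescribed by 20%, from 35% to 55" per cent. The second paragraph then gives the calculation that the trial used. It is designed "to detect an improvement of 20% in a certain target between groups", "assuming an ICC of 0.10", with "an alpha of 0.05 and a beta of 0.1 and a mean group size of seven, 44 LQICs would be needed". The recruitment target follows: "Anticipating a dropout of 10%, we would need to recruit 50 groups". The Abstract repeats a figure of about 50 groups. The calculation paragraph does not repeat the rates and does not say whether alpha is one- or two-sided. Under Randomization, "all groups within a stratum will be randomly allocated to either arm A or arm B"; no allocation ratio is given.

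**The concern.** A beta of 0.1 promises 90% power. If the printed inputs do not lead to 44 LQICs at that beta, then either the stated power or the stated number is wrong, or an input was used that the article does not print. The figure matters because it sets the recruitment target and is the only statement of power in the article. A reader who later weighs a result showing no difference would take the chance of missing a 20-point improvement to be 10%. On the printed inputs it would be about twice that with 44 evaluable LQICs.

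**Working it through.** **Inputs.** From Sample size: difference of 20 percentage points; rates p1 = 0.35 and p2 = 0.55 (from the example); ICC 0.10; alpha 0.05; seven GPs per LQIC; 10% dropout. Assumptions: each GP contributes one yes/no observation, the two arms are of equal size, and alpha is two-sided unless noted.

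**Formulas.**
- GPs per arm, pooled variance: n = [z_a × √(2 × 0.45 × 0.55) + z_b × √(0.35 × 0.65 + 0.55 × 0.45)]² / 0.20²
- GPs per arm, unpooled variance: n = (z_a + z_b)² × (0.35 × 0.65 + 0.55 × 0.45) / 0.20²
- Design effect: 1 + (7 − 1) × 0.10 = 1.6
- LQICs per arm: n × 1.6 / 7, rounded up, then doubled

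**Reproducing 44.** With z_a = 1.96 and z_b = 0.8416 (beta 0.2), the pooled formula gives n = 95.9, so 96 GPs per arm. Then 96 × 1.6 / 7 = 21.9, which is 22 LQICs per arm and 44 in total.

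**At the printed beta.** With z_b = 1.2816 (beta 0.1), n = 127.9, so 128 GPs per arm. Then 128 × 1.6 / 7 = 29.3, which is 30 per arm and 60 in total (59 if only the total is rounded up).

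| Beta | Alpha | Variance | GPs per arm | LQICs per arm | Total LQICs |
|---|---|---|---|---|---|
| 0.1 | two-sided | pooled | 128 | 29.3 | 60 |
| 0.1 | two-sided | unpooled | 124.8 | 28.5 | 58 |
| 0.1 | one-sided | pooled | 105 | 24.0 | 48 |
| 0.1 | one-sided | unpooled | 101.7 | 23.2 | 48 |
| 0.2 | two-sided | pooled | 96 | 21.9 | 44 |
| 0.2 | two-sided | unpooled | 93.2 | 21.3 | 44 |

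An arcsine calculation also gives 60 at beta 0.1 and 44 at beta 0.2, two-sided. A continuity correction raises the beta 0.1 figure to 64.

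**Power at the planned numbers, two-sided.** The effective number of GPs per arm is (LQICs per arm) × 7 / 1.6.
- 44 LQICs: 22 × 7 / 1.6 = 96.25; power 80.1% (pooled) or 81.2% (unpooled).
- 50 LQICs, none lost: 25 × 7 / 1.6 = 109.4; power 84.9% (pooled) or 85.9% (unpooled).

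**Dropout step.** 44 / 0.9 = 48.9, so 49, which agrees with 50 for even arms. This step is sound. By the same rule, 58 / 0.9 = 64.4 and 60 / 0.9 = 66.7, so 65 to 67 would be recruited.

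**The case against.** The strongest reply is that the decisive input is inferred. The 35% and 55% belong to an illustration, not to the calculation paragraph, and the result depends heavily on the rates. With unpooled variance, a rise from 15% to 35%, or a fall from 35% to 15%, needs 93.3 GPs per arm; 93.3 × 1.6 / 7 = 21.3, hence 44 LQICs at 90% power (46 with pooled variance). This part stands: it cannot be said that no reading yields 44 at beta 0.1. But the article names no such pair of rates, while the one pair it does name gives 44 at beta 0.2. That makes a wrong beta the likelier explanation without proving it.

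A second reply is that an improvement is directional, so alpha might be one-sided. In that case 44 LQICs give about 88% power and 50 give 91 to 92%. This narrows the gap, but beta 0.1 still needs 48, not 44, and the article does not say that alpha is one-sided.

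A third reply is that the Analysis section plans multilevel covariance analysis of volumes with baseline as a covariate, which may be more efficient than comparing two proportions. That is fair as a comment on the eventual analysis. The calculation takes no credit for such a gain, however, and the article gives no baseline correlation from which to work one out, so it cannot account for the 44.

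Finally, the authors are candid that the calculation is uncertain, in Sample size and again in the Discussion. That caveat concerns unknown targets. It does not reconcile inputs and a result that are both printed.

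**Conclusion.** The passage is wrong as it stands, on the only rates it prints. With 35% to 55%, two-sided alpha 0.05, ICC 0.10 and seven GPs per LQIC, beta 0.1 needs 14 to 16 more LQICs than the stated 44 (58 − 44 = 14; 60 − 44 = 16), and 44 is the number for beta 0.2. This rests on three assumptions that the article does not confirm: that the example rates were the ones used, that alpha is two-sided, and that allocation is 1:1.

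Two stronger readings are tempting and are not supported. One is that the trial has 80% power. That figure belongs to 44 evaluable LQICs under a two-proportion calculation; with all 50 retained it is about 85 to 86%, and the power of the planned covariance analysis cannot be derived from what is printed. The other is that the beta is known to be the misprint. The article shows only that its figures disagree, not which of them is in error.

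**What to change.** State in Sample size the two rates, the sidedness of alpha and the formula that were used, and reconcile beta with the number of LQICs.

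- If 35% to 55% with two-sided alpha was used, restate beta as 0.2 (80% power) for 44 LQICs.
- If 90% power was intended on those inputs, state that 58 to 60 LQICs, or 65 to 67 with the 10% dropout allowance, would be required and that the planned 50 do not reach it.
- If other rates or a one-sided alpha were used, print them, so that the calculation can be repeated.

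The cost is a few words and one corrected figure. No extra recruitment or change of design is asked for. On the printed rates the stated power becomes less favourable.

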### Analysis

Analysis will be based on the intention-to-treat principle. Data on GPs lost to follow-up will be extracted from the various databases if possible.

We will analyse covariance using test and drug volumes during the intervention period as the dependent variables, and the baseline data and the explanatory variables as independent variables. The analysis will be repeated using proportions stemming from prescription performance indicators, if available. The unit of allocation to the trial is the LQIC. In larger practices with more than one GP, not all volumes of tests ordered and drugs prescribed will be traceable to an individual GP. In these cases, the unit of analysis will be the practice as a whole. Because of this unit of analysis error, the data will be analysed using multilevel modelling. Data on drugs and tests will be clustered to individual GPs at level one, the practice at level two, the LQIC at level three and the region at level four.

The nature of this study makes it difficult to blind the participants, except for the tests or drugs serving as controls in the other arm. The data analyst will be blinded for the allocation result. Costs of the intervention will be calculated. A cost-effectiveness analysis will be based on these figures. We will use cost minimization analysis from a societal perspective, assuming that the strategy will reduce redundant testing and prescribing. If there are signs of improvement of care (higher scores on the performance indicators), the impact on health may be estimated by modelling the future gains and benefits. Data include costs of coordinating the strategy by the regional contact group, of preparing feedback reports and of chairing the GP groups. The costs of the entire test ordering strategy by [name] were €554.70 per GP per six months (three meetings). The major part of the cost of this strategy consisted of opportunity costs, *viz *the costs of the GPs' time spent attending the session. Because GPs were already attending these meetings and were financially compensated, it seems fair to ignore the opportunity costs. This results in costs of the test ordering strategy of €92.70. The gains obtained by improving test ordering behaviour were €301.00 per GP per six months. Introducing the test ordering strategy would save €208.30 (92.70 to 301.00) per GP per six months [33]. Because prescribing costs are higher, the cost reductions gained by reducing superfluous prescribing should also be higher.

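### The step from 44 to 50 LQICs corrects for lost data, but dropped-out groups may stay in the analysis; if they stay with little or no effect, 50 falls slightly short of the power of 44

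*Protocol article*

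**What the plan says.** The Sample size section of the protocol article sets out "to detect an improvement of 20% in a certain target between groups", with "assuming an ICC of 0.10 [5"] and "an alpha of 0.05 and a beta of 0.1 and a mean group size of seven, 44 LQICs would be needed". An illustration just before it gives the rates: "by 20%, from 35% to 55" per cent. The recruitment target follows: "Anticipating a dropout of 10%, we would need to recruit 50 groups". Dropout is not defined; it could mean leaving the strategy or losing the outcome data.

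The Analysis section commits to intention to treat and adds "Data on GPs lost to follow-up will be extracted from the various databases if possible". Under Extraction of feedback data, prescribing volumes come from health insurers' databases and test volumes from laboratory and diagnostic-centre databases. Neither source depends on a group continuing to meet. The Process evaluation list counts how many groups complete participation, so stopping early is foreseen.

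**The concern.** Dividing by 0.9 is right when 10% of groups disappear and those remaining show the full effect. It is not the matching correction when the 10% stay in the analysis as randomised but respond less. The sample is then not smaller; the mean difference is. Required numbers scale with one over the square of the difference, so the matching divisor with no retained effect is 0.9² = 0.81.

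Routine databases and an intention-to-treat analysis make retention a natural reading of the plan. If it applies, the figure of 50 does not fully protect the power that it is presented as protecting against 10% dropout.

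**Working it through.** **Inputs from the Sample size section.** Rates 0.35 and 0.55 (given as an example and taken here as the basis of the calculation); ICC 0.10; seven per group; alpha 0.05; beta 0.1; 10% dropout. **Assumed, because not stated:** two-sided test, 1:1 allocation, dropout spread evenly over the arms.

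**Design effect.** 1 + (7 − 1) × 0.10 = 1.6.

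**The plan's 44.** The two-proportion formula with pooled variance under the null is n per arm = [z(α/2)·√(2p̄q̄) + z(β)·√(p₁q₁ + p₂q₂)]² / (p₂ − p₁)².

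- 90% power: (1.960 × 0.7036 + 1.282 × 0.6892)² / 0.04 = 128 per arm. 128 × 1.6 / 7 = 29.3 groups per arm, so 58.5 in total, or 60 for equal arms.
- 80% power: (1.960 × 0.7036 + 0.842 × 0.6892)² / 0.04 = 96 per arm. 96 × 1.6 / 7 = 21.9 groups per arm, so 44 in total.

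The stated 44 thus reproduces at 80% power, not at 90%. A one-sided test at 90% gives 48.

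**The step to 50.** 44 / 0.9 = 48.9, so 49, or 50 for equal arms. This step reproduces as simple replacement of lost groups.

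**Power of 50 LQICs under different meanings of dropout.** Effective n per arm = (groups / 2) × 7 / 1.6; for 50 groups, 25 × 7 / 1.6 = 109.4. If dropouts keep a share r of the effect, the difference is 0.20 × [1 − 0.10 × (1 − r)]; with r = 0 it is 0.18, that is 35% against 53%.

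| Scenario | Rates compared | Power (two-sided) |
|---|---|---|
| 44 LQICs, all fully exposed | 35% v 55% | 80.1% |
| 50 recruited, 10% missing (45 analysed) | 35% v 55% | 81.0% |
| 50, dropouts kept, no effect | 35% v 53% | 76.8% |
| 50, dropouts kept, 25% of effect | 35% v 53.5% | 79.1% |
| 50, dropouts kept, 50% of effect | 35% v 54% | 81.2% |
| 50, dropouts kept, 75% of effect | 35% v 54.5% | 83.1% |
| 50, full effect in all | 35% v 55% | 84.9% |

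If half of the zero-effect dropouts are retrieved and half are missing, power is 78.9%.

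Only dropout among groups assigned a topic dilutes that topic's contrast. A group serving as control for the topic does not dilute it by leaving.

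**Break-even with 44 groups.**

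- All dropouts retained: 1 − 0.10 × (1 − r) = √(44/50) = 0.938, so r is about 0.38.
- A share q of zero-effect dropouts retrieved: 50 × 0.81 / (0.9 + 0.1q) = 44, so q is about 0.2.
- Groups needed to match 44 with all retained at zero effect: 44 / 0.81 = 54.3.

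**On the plan's nominal scale.** If 44 groups are taken to give 90%, the standardised difference is 1.960 + 1.282 = 3.242. With 50 groups and a tenth of the effect lost, 3.242 × √(50/44) × 0.9 − 1.960 = 1.15, which is 87.5% power. The dilution loss is then about 2.5 points.

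**One-sided check.** 44 LQICs give 87.9%, and 50 with dropouts kept at no effect give 85.4%, again a loss of about 2.5 points.

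**The case against.** The strongest reply is that the plan does not commit to full retention with no effect. The sentence on extraction concerns individual GPs and applies only where possible. The Discussion warns that extraction may ask too much of some centres, which would lose test data. Where data are lost, dividing by 0.9 is correct and 50 is enough.

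Zero effect in every dropout is also a harsh assumption. Groups work through three topics in turn, so one that leaves late has already had feedback and made agreements. One that leaves before making any agreement has no target of its own, so for the first effect outcome (volumes the group agreed to change) it behaves like a missing group. Finally, the rates are only an example, the article itself doubts that a sample size can be calculated, and the planned analysis is a baseline-adjusted multilevel model of volumes, not a comparison of two proportions.

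Most of this stands, and it makes the point conditional. A reader might infer that 50 LQICs simply fail to restore the power of 44, or that about 55 must be recruited. The document does not support that, because the shortfall disappears once retained dropouts keep about 38% of the effect, or if no more than about a fifth of zero-effect dropouts are retrieved. What remains is that the allowance is built on one meaning of dropout while the Analysis section aims, where it can, at another.

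**Conclusion.** The point holds in conditional form and is small. With 10% dropout, 50 LQICs give about 77% power if all dropouts are kept with no effect, and about 81% if they are missing or keep half the effect, against 80% for 44 fully exposed groups. The worst-case cost of dilution is about 3 percentage points, or about 2.5 on the nominal 90% scale. These figures rest on the example rates, a two-sided test, 1:1 allocation and a simple two-proportion comparison, so they show the size of the problem and do not predict the power of the planned model.

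A reader might also attribute the whole distance from the stated 90% to 77% to dropout. That would be wrong. About 10 of those 13 points arise because 44 groups give roughly 80%, not 90%, on the stated inputs. That discrepancy is separate and larger, and it exists before any dropout.

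**What to change.** In the Sample size section, say whether dropout means leaving the strategy or missing outcome data, and state that groups that leave are analysed as randomised wherever their data can be obtained. Restate the power of 50 recruited LQICs with 10% dropout as about 77% to 81% on the example rates: 77% if all are retained with no effect (an 18-point difference), 81% if they are missing or keep half the effect. Report separately that 44 groups correspond to about 80% power on these inputs and not to the 90% implied by beta 0.1, so that dilution is not blamed for that gap.

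The cost is a few sentences and a less favourable figure. This point calls for no extra recruitment and no change to the design or analysis.
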